**Primary outcome**	
3-year freedom from MALEs	Free of type IB, III endoleak and limb occlusion within 3 years
**Secondary outcomes**	
3-year freedom from type IA endoleak	Free of type I endoleak within 3 years
3-year freedom from aortic reintervention	Free of any reintervention related to the index EVAR within 3 years
**Other outcomes**	
**Intraoperative technical outcome**	
technical success rate	Freedom from surgical conversion or mortality, type I or III endoleaks, or graft limb obstruction after the deployment of devices
**Short-term postoperative outcomes**	
Acute kidney injury	Serum creatinine elevates by 0.3 mg/dL or 50% compared with baseline within 48 h; or urine less than 0.5 mL/kg/h for more than 6 h
30-day morbidity	The existence of any adverse event within 30 days, consisting of infection, pseudoaneurysm, deep venous thrombosis, hypoalbuminemia, hemorrhage, embolism, stroke, buttock ischemia and systematic complications such as pulmonary, cardiac, cerebral and bowel events
30-day MACEs	Diagnosed with myocardial infarction, chronic cardiac failure, or receive repeat revascularization or died within 30 days

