### Allocations of intervention

Based on the anatomic features of the aneurysm by intraoperative imaging, surgeons will determine whether to adopt CL or SL configuration. When both configurations are feasible, surgeons will assign the limb configuration based on covariate adaptive matching between the two groups. The major matched covariates are as follows: age, gender and aneurysm diameter. Both surgeons and participants are not blinded to the interventions, and only statisticians who analyze the data are blinded.

The CL and SL configurations are defined as crossed or uncrossed limb grafts in anteroposterior view of the final angiogram, respectively. CL is further subdivided into anterior-posterior (AP) cross and left-right (LR) cross, which correspond to ≥ 50 and < 50% overlapped areas between two limb grafts in the angiogram. SL is similarly subdivided into AP parallel and LR parallel with the same definition.

The included patients will receive the same perioperative management, including blood pressure control, analgesia and medication with antiplatelets and statins. In interventional operating room, both common femoral arteries will be used for percutaneous or cut down access. After administration of 0.5 mg/kg unfractionated heparin, graft stents are placed in accordance with instruction for use by an experienced surgeon of vascular surgery. Treatment procedures are performed under a standard protocol. The Endurant II or IIs Stent Graft (Medtronic, Minneapolis, Minn) is used for repair.

Postoperative medications include antiplatelet monotherapy (aspirin 100 mg once a day or clopidogrel 75 mg once a day) and statins. Patients are expected to take these medications all life unless severe adverse event occurs. Anticoagulants, such as low molecular weight heparin or direct oral anticoagulants, will be used according to surgeons’ decision.

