### Follow-up

After the procedure, all included patients will receive follow-up in outpatient clinics at 1, 6, and 12 months and annually thereafter. The required routine examinations include history taking, physical examination, blood biochemical index and duplex ultrasound. All biological specimens will be processed in routine procedure and not be used in ancillary or other studies. The computed tomography angiography will be performed to search for detailed information if any adverse event, especially endoleak or limb thrombosis, is found by duplex ultrasound. Patients who are unable to return to the outpatient clinic will be suggested to undergo duplex ultrasonography or computed tomography in local medical institutions, which will send medical records and images back to researchers. For patients who fail to finish the expected follow-up, telephone interview or WeChat message will be used instead to record survival status and postoperative adverse events. Due to no additional harm induced by the trial, all adverse events will be processed according to normal treatment procedure and patients will not automatically quit the group or receive additional compensation.

Patients are defined as dropout if the following events occur: (1) Fail to complete the expected follow-up and could not obtain image or medical records: a subject is considered lost to follow-up if they could not be contacted *via* five attempts by telephone or WeChat message. (2) Make withdrawal consent: all participants have the right to withdraw from the study at any time for any reason without obstruction.

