### Outcomes of interest

The primary outcome is 3-year freedom from MALEs, which involves type IB/III endoleak and limb occlusion. Type IB endoleak is defined as persistent direct flow in the aneurysm sac due to inadequate distal seal of the stent graft. Type III endoleak is defined as persistent direct flow resulting from stent graft component separation or fabric tear. Limb occlusion is defined as a total occlusion occurring in limb grafts, regardless of symptoms, or an invasively treated stenosis resulting from thrombus formation (> 50% lumen reduction).

The secondary outcomes involve 3-year freedom from type IA endoleak and 3-year freedom from aortic reintervention. Type IA endoleak is defined as persistent direct flow in the aneurysm sac due to inadequate proximal seal of the stent graft. Aortic reintervention refers to any secondary surgical procedure related to the index EVAR.

Other outcomes consist of three aspects: intraoperative technical outcomes (operation time, radiation exposure time, dosage of contrast medium and technical success rate); short-term postoperative outcomes (length of stay in intensive care unit or vascular ward, acute kidney injury, 30-day overall morbidity, 30-day major adverse cardiac events, 30-day all-cause mortality); long-term outcomes (renal function decline, occurrence of type I/II/III endoleak or stent migration, freedom from major adverse cardiac events, aneurysm related death, overall survival).

Detailed information for outcomes is listed in Table 2.

**TABLE 2 T2:** Detailed information for outcomes.

Outcomes	Definition

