**Long-term outcomes**	
Renal function decline	Diagnosed with chronic renal failure and could not be attributed to other known causes
Type I endoleak	Endoleak due to inadequate proximal or distal seal of the stent graft
Type II endoleak	Endoleak originating from collateral vessels
Type III endoleak	Endoleak resulting from stent graft component separation or fabric tear
Stent migration	Migration from original position for more than 5 mm
Aneurysm related death	All deaths from secondary aneurysm rupture after repair, death within 30 days of any reintervention attributable to the aneurysm or death from other aneurysm-related causes (including graft infection or fistula)

MALEs, major adverse limb-graft events; EVAR, endovascular aneurysm repair; MACEs, major adverse cardiac events.

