### Data collection

Figure 1 shows the flow diagram of the trial. Once patients are admitted, baseline data will be collected for both groups, including demographic characteristics, comorbidities and anatomical variables. The demographics are collected from history taking and hospital information system. The comorbidity is evaluated by the Charlson Comorbidity Index to quantify its severity. Anatomical variables are as follows: length of aneurysm neck, oversizing ratio in proximal neck and distal limb, neck angulation, maximum diameter of aneurysm sac, intramural thrombus load of aneurysmal sac, iliac tortuosity, common iliac artery aneurysm and distal iliac calcification. We will report reasons for withdrawal for each group and compare the reasons qualitatively. Details of the procedure, consisting of operation time, radiation exposure time and contrast medium dosage, are recorded immediately after the operations. At preoperative and postoperative evaluation (24, 48, and 72 h), laboratory examinations will be conducted and corresponding results will be collected from the laboratory information system.

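### Renal function decline is defined by an attributed diagnosis with no comparison to baseline, and the AKI creatinine rule stops before the 72 h laboratory result: a cheap improvement to two lower-ranked outcomes

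*Protocol article*

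**What the plan says.** The Outcomes of interest section of the protocol article puts both renal outcomes in its third tier ("Other outcomes consist of three aspects: intraoperative technical outcomes", followed by short-term and long-term outcomes) and refers the reader to Table 2 for definitions.

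- **Renal function decline** (Table 2, Long-term outcomes): "Diagnosed with chronic renal failure and could not be attributed to other known causes". No creatinine or eGFR threshold, reference value, assessment time or assessor is given.
- **Acute kidney injury** (Table 2, Short-term postoperative outcomes): "Serum creatinine elevates by 0.3 mg/dL or 50% compared with baseline within 48 h", with a second route, "or urine less than 0.5 mL/kg/h for more than 6 h".

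The measurement schedule is set elsewhere. Data collection states: "At preoperative and postoperative evaluation (24, 48, and 72 h), laboratory examinations will be conducted". Follow-up states that "all included patients will receive follow-up in outpatient clinics at 1, 6, and 12 months and annually thereafter", and "The required routine examinations include history taking, physical examination, blood biochemical index and duplex ultrasound". On blinding, Allocations of intervention states: "Both surgeons and participants are not blinded to the interventions, and only statisticians who analyze the data are blinded".

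**The concern.** An outcome called decline should record a change, and this one does not. It records whether a diagnosis was made and whether someone judged that nothing else explained it. The treating team knows the configuration and, in this non-randomized study, also chose it. With no rule for the judgement, two assessors could score the same patient differently.

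The AKI rule has a smaller fault. It combines an absolute and a relative creatinine rise but gives both the same 48 h limit, so the relative criterion does little work and the last scheduled perioperative laboratory result cannot count towards the creatinine rule.

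What is at stake is how informative the renal safety comparison will be. The trial's hypothesis covers safety in the short and long term, and contrast dose and operation time are recorded outcomes. The Introduction cites two retrospective cohorts in which crossed limb procedures took longer, although the same cohorts found postoperative complications comparable.

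**Working it through.** The article gives no AKI rate, no renal-decline rate and no timing of renal events, so there is no plan figure to reproduce. The check sets the definitions against the schedule and adds a short piece of arithmetic.

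**Renal function decline**

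1. *Patients with chronic renal failure at entry.* The exclusions in Table 1 are intolerance of contrast agents, antiplatelets or anticoagulants, and previous aneurysm repair. Chronic renal failure as such is not excluded, so these patients can be enrolled. They already hold the diagnosis, and the definition does not say whether they are events from the start, never events, or outside the analysis. Further loss of function in them has no defined place.
2. *Patients who lose function but do not reach the diagnosis.* They are non-events however large the fall, because nothing is compared with the preoperative value.
3. *Patients newly diagnosed who have another possible cause.* Their status turns on the attribution clause. The article gives no rule for it, and only the statisticians are blinded, so whoever makes the judgement may know the configuration.
4. *What is available instead.* Blood biochemistry is required at each routine visit. Within the 3-year horizon these are months 1, 6, 12, 24 and 36 (Abstract, Methods). None of these results enters the definition. Creatinine is not named in the panel; that it is included is likely but is an inference.

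**Acute kidney injury**

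The 48 h is read as running from the procedure, since the comparison is with baseline.

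1. *When does the 50% criterion add a case?* Let B be baseline creatinine in mg/dL. A 50% rise equals 0.5 × B. It already meets the absolute criterion when 0.5 × B ≥ 0.3, that is B ≥ 0.3 / 0.5 = 0.6. With one shared window, the 50% criterion adds cases only when B is below 0.6 mg/dL.
2. *Which scheduled results can count?* Of the three postoperative times, 24 h and 48 h fall inside the creatinine window and 72 h falls outside. One of three cannot meet the creatinine rule.
3. *Illustration with invented values.* Baseline 1.0, 48 h value 1.25, 72 h value 1.6 mg/dL.
   - At 48 h: 1.25 − 1.0 = 0.25 mg/dL, or 25%. Neither criterion is met.
   - At 72 h: (1.6 − 1.0) / 1.0 = 60%. Above 50%, but outside the window.
   - The creatinine rule is not met. The patient is still an AKI case if the urine criterion is met, because that route has no 48 h limit of its own.

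**The case against.** The strongest reply has five parts.

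- **Rank.** Both outcomes sit in the third tier. The primary outcome and the sample size concern limb events, and no renal non-inferiority test is specified. This stands, and it limits the weight of the point.
- **No contradiction in the AKI rule.** A reader might infer that a 48 h window conflicts with a 72 h laboratory panel. It does not. The article does not say the 72 h panel is taken to detect AKI, and the 24 h and 48 h results serve the rule as written. Redundancy between two criteria joined by *or* also loses no case in itself. The point here is a better use of a scheduled result, not an error.
- **Creatinine is not named.** A reader might take it as given that the trial measures creatinine at 72 h and at every visit. The article speaks only of laboratory examinations and a biochemical index. The perioperative inference is strong, because the AKI rule needs creatinine. The follow-up inference is plausible but should be confirmed.
- **A measured endpoint will have gaps.** Under Follow-up, patients who cannot return are advised to have ultrasound or CT locally, with no blood test mentioned, and others are reached by telephone or WeChat. A diagnosis can still be captured from them; an eGFR cannot. This stands, and the fix must allow for it.
- **An article condenses.** Handling of baseline renal disease and the eGFR formula may be in a fuller document. That is fair for those details. It does not cover the core of the definition, which Table 2 states outright.

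**Conclusion.** The point holds as a modest, inexpensive improvement to two lower-ranked outcomes. Its main part is renal function decline: as written, the outcome measures no decline, leaves patients with chronic renal failure at entry unclassified, misses falls short of the diagnosis, and depends on a judgement of cause that is not blinded. The AKI part is minor: the relative criterion adds nothing at a baseline of 0.6 mg/dL or more, and one of three scheduled postoperative results cannot meet the creatinine rule.

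Two stronger conclusions are tempting and are not supported. A reader might infer that most true declines would be lost, since older vascular patients often have another candidate cause. The article gives no comorbidity prevalence and no renal event rate, and a possible cause is not the same as an attributed one, so the loss cannot be sized. A reader might also infer that the definitions push the comparison towards no difference. Missing events at similar rates in both groups would shrink an absolute difference, but unblinded attribution can favour either group, so the net direction is unknown.

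The verdict rests on reading the 48 h as counted from the procedure. The proposed remedy also assumes that creatinine is part of the scheduled panels.

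**What to change.** **Renal function decline.** Replace the definition with a prespecified change in creatinine or eGFR from the preoperative value at the scheduled visits, for example a fall in eGFR of 30% or more. State the threshold, formula and visits. Drop the attribution clause from the definition and report attributed cause separately as a description. Name creatinine in the follow-up panel. Keep a diagnosis of chronic renal failure from records or interview as a supportive measure.

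*Cost:* one line in Table 2, and probably no new samples if creatinine is already in the panel. Values will be missing for patients followed locally, by telephone or by WeChat, and the extent of this should be reported by group.

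**Acute kidney injury.** Keep the 0.3 mg/dL rise within 48 h and the urine criterion unchanged, and let the 50% rise use the highest creatinine up to 72 h. The article should at least say whether the 72 h result counts.

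*Cost:* one line in Table 2. The revised rule contains the present one, so AKI counts can only stay the same or rise, probably slightly. Comparability falls with any earlier data collected under the present definition.

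### Two of the other outcomes in Table 2, 30-day MACE and long-term renal function decline, rest on chronic diagnoses with no new-onset or baseline-change criterion and should be reworded

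*Protocol article*

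**What the plan says.** The Outcomes of interest section lists these outcomes in its third tier, below the primary and secondary outcomes. Table 2 of the protocol article gives the definitions.

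- **30-day MACE:** "Diagnosed with myocardial infarction, chronic cardiac failure, or receive repeat revascularization or died within 30 days".
- **Long-term MACE:** the text lists "freedom from major adverse cardiac events, aneurysm related death, overall survival" among the long-term outcomes, but Table 2 has no long-term MACE row.
- **Renal function decline (long-term):** "Diagnosed with chronic renal failure and could not be attributed to other known causes".
- **Acute kidney injury (short-term):** "Serum creatinine elevates by 0.3 mg/dL or 50% compared with baseline within 48 h", or low urine output.
- **30-day morbidity:** any adverse event within 30 days, including "systematic complications such as pulmonary, cardiac, cerebral and bowel events".

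On the data available, the Data collection section says "At preoperative and postoperative evaluation (24, 48, and 72 h), laboratory examinations will be conducted" and "The comorbidity is evaluated by the Charlson Comorbidity Index to quantify its severity". The Follow-up section says "The required routine examinations include history taking, physical examination, blood biochemical index and duplex ultrasound". The exclusions in Table 1 are intolerance of contrast, antiplatelets or anticoagulants, and previous aneurysm repair. According to the section on allocation, surgeons and participants are not blinded; only the statisticians who analyse the data are.

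**The concern.** The other three components of the 30-day composite (infarction, repeat revascularization, death) are events that happen after the operation. Chronic heart failure is a state that a patient may bring to the operation, while the form of heart failure that a procedure could provoke within 30 days is acute or decompensated. The row names the first and omits the second.

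The renal row has a related fault. Its label promises a change, but its definition asks for a diagnosis, so a decline that stops short of that diagnosis is not counted. The clause on other known causes calls for a judgement, and the protocol gives no rule for making it and does not say that whoever makes it is blinded.

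At stake is how well these two outcomes can describe cardiac and renal safety. The stated hypothesis covers safety as well as efficacy. The Introduction cites two cohorts with longer procedures in the crossed-limb group, and contrast dose is itself an outcome. A reader will therefore look at these rows for a difference.

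**Working it through.** The point concerns definitions, so there is no plan figure to reproduce. The relevant rows of Table 2 compare as follows.

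| Outcome | What must be observed | Compared with baseline? | New or worsening required? |
|---|---|---|---|
| Acute kidney injury | Measured creatinine rise or low urine output | Yes, for creatinine | Yes, for creatinine (a rise) |
| 30-day MACE, heart-failure part | Diagnosis of chronic heart failure | No | Not stated |
| Long-term MACE | No row in Table 2 | Not stated | Not stated |
| Renal function decline | Diagnosis of chronic renal failure, no other known cause | No | Not stated |

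Five hypothetical patients show what the wording does.

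1. *Acute heart failure on day 3, no infarction or revascularization, survives.* Not a MACE as written. It counts only in 30-day morbidity, pooled with events such as infection and hypoalbuminemia.
2. *Known chronic heart failure before surgery, uneventful course.* Not a MACE if the row means a diagnosis first made within 30 days; a MACE if it means carrying the diagnosis in that window. The text does not decide, and Table 1 allows the patient in.
3. *Creatinine well above the preoperative value at two years, no diagnosis of chronic renal failure.* Not renal function decline.
4. *Chronic renal failure before surgery.* The word decline and the attribution clause point towards not counting it. No rule says so, and no rule says whether such a patient is at risk.
5. *Chronic renal failure first diagnosed at two years in a patient with another renal risk factor.* Counted or not according to an attribution judgement without criteria.

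Patients 1 and 3 follow from the plain wording. Patients 2, 4 and 5 are ambiguities that two careful coders could resolve differently.

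**Can the direction of bias be derived?** The Statistical analysis section uses odds ratios for short-term outcomes. Assume, purely for illustration, true 30-day MACE rates of 4% (crossed) and 2% (standard), and add pre-existing heart failure as if every case were counted, without overlap. The odds ratio is [p1/(1−p1)] / [p2/(1−p2)].

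- No contamination: (0.04/0.96)/(0.02/0.98) = 2.04; risk difference 2 points.
- 7.5 points added to both arms: (0.115/0.885)/(0.095/0.905) = 1.24; risk difference still 2 points.
- 10 points added to crossed, 5 to standard: (0.14/0.86)/(0.07/0.93) = 2.16; risk difference 7 points.
- 5 points added to crossed, 10 to standard: (0.09/0.91)/(0.12/0.88) = 0.73; risk difference −3 points.

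The result depends on the effect scale and on the balance of baseline disease between the arms. The documents give no prevalence or event rate for either arm, so neither size nor direction can be derived from them.

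**The case against.** The strongest reply is that the protocol already covers much of this. Acute kidney injury is an acute renal outcome measured against baseline. Acute heart failure is not lost to the trial, because 30-day morbidity includes cardiac events. A diagnosis within 30 days, under a heading for postoperative outcomes, reads naturally as a new one. Pre-existing renal disease is an obvious other known cause. The only hypothesis with a margin and a sample size concerns adverse limb events.

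All of that stands, and it limits the point. It does not repair the two rows: MACE as a named outcome still omits acute heart failure, and long-term renal decline still has no baseline criterion.

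A reader might infer three stronger things that the documents do not support.

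- **That the cardiac and renal outcomes in general are chronic diagnoses.** The acute kidney injury row and three of the four MACE components are not.
- **That these faults all favour a finding of non-inferiority.** These outcomes have no margin. The illustration also shows that equal contamination dilutes an odds ratio but leaves the risk difference unchanged, while unequal contamination can act either way.
- **That pre-existing disease would outnumber real events.** With an assumed heart-failure prevalence of 5–10%, there would be 73 × 0.05 = 3.7 to 73 × 0.10 = 7.3 crossed-limb patients, and 202 × 0.05 = 10.1 to 202 × 0.10 = 20.2 standard-limb patients. With an assumed true MACE rate of 2–4%, the crossed arm would have 73 × 0.02 = 1.5 to 73 × 0.04 = 2.9 real events. This is a worst case: neither rate is in the documents, and it requires every pre-existing case to be coded as an event.

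**Conclusion.** The concern holds for two rows of Table 2. By its literal wording, the 30-day MACE definition leaves out acute or decompensated heart failure, and it does not clearly keep out heart failure that was already present; long-term MACE may inherit both problems. Long-term renal function decline ignores any change from the preoperative value that falls short of a chronic renal failure diagnosis, and it leaves attribution to an unspecified judgement.

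The consequence is limited to the interpretation of these other outcomes. The primary outcome, secondary outcomes and sample size are untouched. The size and direction of any bias cannot be determined from the documents. The conclusion rests on the article's wording and on the assumption that Table 2 is what event coders will apply.

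**What to change.** In Table 2:

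1. Replace the chronic heart-failure component with new or worsening heart failure after the index procedure, and state that the same wording applies to 30-day and long-term MACE.
2. Define renal function decline as a prespecified change in creatinine or eGFR from the preoperative value, using the follow-up biochemistry. Confirm first that this panel includes creatinine, because the Follow-up section does not name it.
3. Treat patients with end-stage renal disease at baseline as not at risk for this outcome.
4. The attribution clause need not be dropped, since it may keep out renal failure unrelated to the procedure. If it is kept, report attribution as a secondary classification beside the unattributed count.

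The cost is the rewording of two rows and slightly more event coding. If creatinine is in the follow-up panel, no new data are needed.
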